##### Missing data

Participants with missing data either because of early drop-out, loss to follow-up or missed participation in the data collection can bias the results. By design, no data will be missing at baseline because only participants with complete baseline data will be randomised.

Missing variables in outcome measures will be handled according to instrument developers’ guidelines. As a general rule, if more than 20% of the items of an instrument are missing, the summary score will be assigned as missing. Missing data will be reported as part of the summary presentation of the raw data. Logistic regression will be used to explore whether participants with missing data have different characteristics than the completers or whether missing data can be assumed missing by random.

##### Procedures for data checking and entering

Data will be double data entered, and data validation will take place according to the procedures set out in the data management plan and data validation plan. Prior to any statistical analysis, all variables will be checked for the number of missing values, impossible values and improbable values. Impossible and improbable values will be defined by clinical opinion. Improbable values will also include values that are outside three standard deviations of the mean value. Any questions regarding the data will go back to the data manager. Descriptive statistics will be calculated for all variables, and distributional assumptions will be checked.

The Standard Protocol Items-Recommendations for Interventional Trials (SPIRIT) table provides an overview of the study conduct, review, reporting and interpretation and is presented in Table 2. The final report will follow the Consolidated Standards of Reporting Trials (CONSORT), as well as the Template for Intervention Description and Replication (TIDieR).

**Table 2 Tab2:** The Standard Protocol Items-Recommendations for Interventional Trials (SPIRIT)

Section/item	Item No	Description	Addressed on page number

**Introduction**			
Background and rationale	6a	Oesophagogastric cancers are a considerable health burden. In the past 10 years the 5-year survival for both cancers has doubled. This is due to a number of factors including advances in neoadjuvant and adjuvant chemotherapy and radiotherapy. However, physical fitness significantly declines as a result of neoadjuvant and adjuvant therapy. From studies in other cancers, perioperative training is known to improve physical fitness, yet little research has been performed on its effects in those with upper oesophagogastric cancers. Therefore, the aim of the PERIOP-OG trial is to investigate the effects of a community-based exercise training programme (delivered in a leisure centre or at home, depending on the patient location) pre- and post–operatively compared to usual care on cardiorespiratory fitness and other physical, psychological and clinical health outcomes in people with confirmed oesophagogastric cancer.	5
	6b	The usual-care control group (usual care – no formal exercise training) receive routine care throughout their cancer pathway from diagnosis to surgical resection. No specific advice about exercise training is offered.	9
Objectives	7	The aims of this study were to evaluate the following hypotheses: Primary hypothesis: A structured community-based exercise programme compared with a usual care control group (usual care – no formal exercise training) will result in a clinically significant increase in cardiorespiratory fitness assessed using a 6-min walk test between the baseline and the pre-surgery time point. Secondary hypotheses: A structured community-based exercise programme compared with a usual care control group (usual care – no formal exercise training) will result in improvements in other physical health outcomes assessed using upper and lower body strength test, activity behavior monitoring, body mass index, frailty, and psychological health questionnaires assessed at 5 time points baseline, post NCT, pre-surgery, 4 weeks and 10 weeks after surgery as well as semi-structured interviews assessed pre and post-surgery. Exploratory Endpoints: Post-operative morbidity, comprehensive complication index, hospital length of stay, nutritional status, immune and inflammatory markers, cancer staging, response to NCT and a medico-economics analysis of cost effectiveness of the exercise intervention on reducing health care costs and burden additionally rates of NCT toxicity, tolerance and complicance will be measured.	7
Trial design	8	Parallel group randomised 1:1 controlled multi-centre trial.	9
**Methods: Participants, interventions, and outcomes**			
Study setting	9	Three Irish Health Services Executive (HSE) hospitals are recruiting to this trial: Beaumont Hospital Dublin, Mercy University Hospital Cork (MUHC) and University Hospital Galway (UHG). Assessments and exercise training are being delivered at several sites. For Beaumont hospital Dublin: ExWell Medical; for MUHC, to cater for a large area: Cork Leisure World, Waterford Institute of Technology, Heartwise for Health and the University of Limerick; and for UHG, Cancer Care West gym.	7
Eligibility criteria	10	Eligibility criteria for inclusion at cancer diagnosis include the following: age ≥ 18 years, with multidisciplinary team (MDT) referral for neoadjuvant chemotherapy or neoadjuvant chemoradiotherapy (NCT) prior to planned oesophagectomy or gastrectomy; with confirmed MDT evidence of adenocarcinoma or squamous cell cancer of the oesophagus, oesophago-gastric junction or stomach requiring planned surgical resection; with recorded measurement (endoscopic or otherwise) that the tumour starts more than 5 cm below crico-pharyngeus. Exclusion criteria include the following: inability to give informed consent; inability to participate in exercise training (unable to perform 6MWT); patients with high-grade dysplasia (squamous cell or adenocarcinoma), distant metastatic disease at time of enrolment or during their NCT therapy, or showing evidence of previous/concomitant malignancy that would interfere with this treatment protocol; or pregnancy.	8
Interventions	11a	Participants are randomised (1:1) to either a structured exercise training programme or usual care control group at baseline	9
	11b	The intervention will be discontinued for a given participant should they no longer wish to participate.	10
	11c	Strategies to improve adherence to intervention protocols include the following: the participants will meet the instructors face to face at the structured exercise sessions, and in addition, they will receive phone calls from the team to monitor their progress and answer any questions they may have on a regular basis.	10
	11d	All routine cancer care is permitted for both groups	9
Outcomes	12	The primary endpoint is cardiorespiratory fitness measured by the 6-min walk test between the baseline assessment and the pre-surgery time point. Secondary endpoints include the measurement of cardiorespiratory fitness, physical health assessed using upper and lower body strength tests, activity behaviours, body mass index, and frailty; and psychological health assessed using health-related quality of life questionnaires and semi structured interviews. Exploratory endpoints include post-operative morbidity, comprenhensive complication index, hospital length of stay, nutritional status, immune and inflammatory markers, cancer staging, response to NCT, medico-economics analysis of cost effectiveness of the exercise intervention on reducing health care costs and burden additionally rates of NCT toxicity, tolerance and compliance.	13
Participant timeline	13	Outcome measurements are taken for all participants at baseline, post-NCT, pre-surgery, 3 days post-surgery, 5 days post-surgery, 4 weeks post-surgery and 10 weeks post-surgery.	7
Sample size	14	The sample size calculation was based on results from the Minnella et al. study, which identified a pre-operative score gain in 6 MWT of 60 m from a baseline score of 450 m (standard deviation 85 m), which is an approximate 13% improvement. Assuming a similar baseline score, a 15% score gain can be detected with *p* value of 0.05 and power 80% with a sample of 26 participants with full data in two groups. With an anticipated 20% drop-out, recruitment of 62 participants is anticipated.	18
Recruitment	15	Inclusion of three clinical sites and seven exercise sites with the additional option of a home programme.	7
**Methods: Assignment of interventions (for controlled trials)**			
Allocation			
sequence generation	16a	Randomisation is performed using a central data management to generate a random allocation sequence (1:1).	9
Allocation concealment mechanism	16b	Randomization allocation is stored in opaque envelops at the lead exercise site (ExWell Medical, Dublin).	9
Implementation	16c	Randomisation is generated by the lead coordinator and exercise lead (LL).	9
Blinding (masking)	17a	Due to the nature of the intervention, blinding of patients or psysiological assessors is not possible. Treating surgeons and their teams are blinded to randomisation as is the primary analyst.	9
	17b	Unblinding will not be permissible	9
**Methods: data collection, management, and analysis**			
Data collection methods	18a	The outcomes are listed in Table 1: Outcomes and assessment measures.	13
	18b	The participants are contacted by telephone during the intervention to promote participant retention and complete follow-up. Baseline data to be collected for participants who discontinue or deviate from intervention protocols, unless they withdraw consent.	13
Data management	19	Data will be double data entered, and data validation will take place according to the procedures set out in the data management plan and data validation plan. Prior to any statistical analysis, all variables will be checked for the number of missing values, impossible values and improbable values. Impossible and improbable values will be defined by clinical opinion. Improbable values will also include values that are outside three standard deviations of the mean value. Any questions regarding the data will go back to the data manager. Descriptive statistics will be calculated for all variables, and distributional assumptions will be checked.	20
Statistical methods	20a	The analysis will be performed as an intention-to-treat analysis. No interim analysis will be conducted. Data validity will be conducted prior to analysis and corrected as appropriate. This includes tabulation of discrete score values and graphical representation of continuous variables (e.g., histograms and box plots). The study population will be described separately for two randomised groups using variables obtained at baseline. The variables will be described as mean (SD) and numbers (%) as appropriate. The primary analysis of the primary outcome will be conducted as t-tests of independent group mean differences in 6MWT at each time point. The mean difference and 95% confidence interval will be reported and illustrated graphically. Individual change in 6MWT will be calculated from baseline and compared at different time points using t-tests. In addition, binary outcome variables indicating ability to walk more than the combined median distance at baseline will be constructed, and the group distribution will be tested at different time points using chi-squared tests.	18
	20b	The secondary analysis of the primary outcome will use mixed-level analysis with intervention group, time point and interaction of intervention and time points. This analysis will include baseline score for the outcome measure as covariate. The estimated parameter for the interaction variables will be interpreted as the difference-in-difference between the two groups over time. A separate analysis will explore potential differences in the intervention group between participants who received the intervention at a training centre and those who trained at home. This analysis will be expanded to include descriptive baseline variables such as sex and age. The secondary analysis will use mixed-level analysis and include baseline score and baseline characteristics as covariates. The cost-effectiveness analysis will be conducted from a societal perspective over the duration of the trial period. No extrapolation of long-term economic outcomes is planned. The EQ-5D-5 L data reported at each time point will be used to estimate quality-adjusted life years using time-weighted utility scores. The utility scores will be calculated for each individual at each data point using the Irish scoring algorithm for EQ-5D-5. The area under the curve denotes the QALY, and incremental QALY is determined as the mean group difference. Cost of the intervention and subsequent resource use will be calculated for each individual using average cost per participant for the intervention programme and self-reported data on healthcare utilisation. Unit costs will be obtained from national sources and assigned to the resource utilisation and aggregated over the whole trial period for each individual. Net monetary benefit (NMB) will be estimated as the cost minus the QALY gain multiplied by an assumed threshold value per QALY. The NMB estimates will also be analysed using regression methods to account for variation in group characteristics and to identify sub-populations where the intervention might have an incremental cost-effectiveness ratio.	
	20c	Participants with missing data, because of early drop-out, loss to follow-up or missed participation in the data collection, can bias the results. By design, no data will be missing at baseline because only participants with complete baseline data will be randomised. Missing variables in outcome measures will be handled according to instrument developers’ guidelines. As a general rule, if more than 20% of the items of an instrument are missing, the summary score will be assigned as missing. Missing data will be reported as part of the summary presentation of the raw data. Logistic regression will be used to explore whether participants with missing data have different characteristics than the completers or whether missing data can be assumed missing by random. If a pattern in missing data can be observed, missing data will be handled using “multiple imputation” techniques where missing variables are predicted in multiple dataset using descriptive variables identified as important covariates for missing data (sex, age, intervention group and baseline score).	19

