### Participants

Eligibility criteria include the following: age ≥ 18 years, multidisciplinary team (MDT) referral for neoadjuvant chemotherapy or neoadjuvant chemoradiotherapy prior to oesophagectomy or gastrectomy; confirmed adenocarcinoma or squamous cell cancer of the oesophagus, oesophago-gastric junction or stomach; and if oesophageal cancer, then the tumours must be more than 5 cm below the crico-pharyngeus muscle.

Exclusion criteria include the following: inability to give informed consent, inability to participate in the exercise training (unable to perform 6MWT), patients undergoing primary surgery, distant metastatic disease, or previous or concomitant malignancy that would interfere with this treatment protocol and pregnancy.

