### Recruitment and randomisation

The PERIOP-OG trial is currently recruiting (start date 1 March 2019, proposed end date July 2020). All potentially eligible patients are identified in each centre’s MDT and are approached for inclusion at diagnosis before NCT has started. Eligible patients are given an information leaflet and then are contacted 72 h later to confirm participation. A baseline assessment visit is then scheduled whereby informed consent is taken, and the randomisation group revealed. Participants are randomised using central data management to generate a random allocation sequence (1:1). Due to the nature of the study, blinding of patients, data collectors and physiological assessors is not possible but the treating surgeons and their teams are blinded to randomisation, as is the primary analyst.

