##### Statistical analysis

The analysis will be performed as an intention-to-treat analysis. No interim analysis will be conducted. Data validity will be conducted prior to analysis and corrected as appropriate.

The study population will be described separately for the two randomised groups using variables obtained at baseline. The variables will be described as mean (SD) and numbers (%) as appropriate.

The primary analysis of the primary outcome will be conducted using t-tests of independent group mean differences in 6MWT. The mean difference and 95% confidence interval will be reported and illustrated graphically. Individual change in 6MWT will be calculated from baseline and compared at different time points using t-tests.

The secondary analysis of the primary outcome will use mixed-level analysis with intervention group, time point and interaction of intervention and time points. This analysis will include baseline score for the outcome measure as a covariate. The estimated parameter for the interaction variables will be interpreted as the difference-in-difference between the two groups over time. A separate analysis will explore potential differences in the intervention group between participants who received the intervention at a training centre and those who trained at home. This analysis will be expanded to include descriptive baseline variables such as sex and age. The secondary analysis will use mixed-level analysis and include baseline score and baseline characteristics as covariates.

The cost-effectiveness analysis will be conducted from a societal perspective over the duration of the trial period. No extrapolation of long-term economic outcomes is planned. The EQ-5D-5 L data reported at each time point will be used to estimate quality-adjusted life years using time-weighted utility scores. The utility scores will be calculated for each individual at each data point using the Irish scoring algorithm for EQ-5D-5 L [47]. The area under the curve denotes the QALY, and incremental QALY is determined as the mean group difference.

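### SPIRIT items 18b and 10 conflict with the stated intention-to-treat analysis and with other parts of the article; followed as written, they permit loss of outcomes after randomisation

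*Protocol article*

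**What the plan says.** **Analysis principle.** The Statistical analysis section states: "The analysis will be performed as an intention-to-treat analysis". SPIRIT item 20a repeats it.

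**Follow-up.** Item 13 says: "Outcome measurements are taken for all participants at baseline, post-NCT, pre-surgery", and lists the post-operative visits as well. Item 11b foresees stopping: "The intervention will be discontinued for a given participant should they no longer wish to participate". Item 18b first describes telephone contact to support retention and full follow-up, and then sets the rule for people who stop or depart from the programme: "Baseline data to be collected for participants who discontinue or deviate from intervention protocols, unless they withdraw consent".

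**Eligibility.** The exclusion criteria in item 10 include "distant metastatic disease at time of enrolment or during their NCT therapy". The Participants section of the main text lists "patients undergoing primary surgery, distant metastatic disease, or previous or concomitant malignancy that would interfere with this treatment protocol and pregnancy", with nothing about metastases found later.

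**Timing.** Patients "are approached for inclusion at diagnosis before NCT has started" (Recruitment and randomisation). Item 11a adds: "Participants are randomised (1:1) to either a structured exercise training programme or usual care control group at baseline".

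**Missing data.** The main text and item 20c both say that only participants with complete baseline data are randomised. Item 20c adds multiple imputation if a missingness pattern is seen, with sex, age, group and baseline score as predictors. The main-text section does not mention imputation.

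**The concern.** An intention-to-treat comparison needs outcomes sought from everyone randomised, whether or not they kept to the programme. Item 18b is the specific instruction for participants who stop, and the only data it names are baseline data. A site that follows it would not invite a discontinuer back for the pre-surgery walk test. Only the exercise arm has a programme to stop or deviate from, since controls receive routine care, so the loss would be largely one-sided. How far the rule reaches depends on what counts as a deviation.

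Item 10 raises a second problem. A criterion that can be met only after allocation is a removal from the randomised set, not an entry criterion.

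The stake is the primary endpoint. Outcomes that were never collected cannot be recovered at analysis, and the exercise arm could come to represent those who kept exercising while the result is labelled intention-to-treat.

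**Working it through.** **1. What item 18b can mean.** Baseline data are complete before randomisation (Missing data section, item 20c). Discontinuation comes after randomisation. Nothing at baseline is then left to collect, so the sentence has content only as a limit on later data. The exception for withdrawn consent shows that it addresses people who still consent. That reading contradicts items 13 and 20a.

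**2. What item 10 can mean.** The order is approach before neoadjuvant treatment, randomisation at baseline, then treatment. The second limb of the metastasis criterion can be met only after allocation.

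**3. The plan's own figures.** Inputs: baseline mean 450 m and SD 85 m (item 14), a 15% difference, alpha 0.05, power 80%. Two-sided testing is assumed.
- Target difference: 0.15 × 450 = 67.5 m.
- A two-sample t-test needs 25.9, so 26 per group, which matches the stated 26 read as per group (power 80.2%).
- Recruitment: 52 × 1.2 = 62.4, which matches 62, or 31 per arm.

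**4. Bias from selective loss, true effect zero.** Assume that the tendency to stay in follow-up is normal and has correlation r with the walk distance. If a fraction f of an arm is lost, the mean of those retained shifts by

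shift = r × SD × φ(z_f) / (1 − f),

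where z_f is the normal quantile at f and φ the normal density. For f = 0.10: 85 × 0.1755 / 0.90 = 16.6 m × r. For f = 0.20: 85 × 0.2800 / 0.80 = 29.75 m × r. The bias is the exercise shift minus the control shift. Simulation gave the same values:

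| Loss, exercise / control | r = −0.3 | r = 0 | r = 0.3 | r = 0.5 | r = 0.7 |
|---|---|---|---|---|---|
| 10% / 0 | −5 m | 0 | +5 m | +8 m | +12 m |
| 20% / 0 | −9 m | 0 | +9 m | +15 m | +21 m |
| 20% / 10% | −4 m | 0 | +4 m | +7 m | +9 m |
| 20% / 20% | 0 | 0 | 0 | 0 | 0 |
| 10% / 20% | +4 m | 0 | −4 m | −7 m | −9 m |

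For exercise-only loss with r from 0.3 to 0.7, the bias is 7% to 31% of the 67.5 m target (5/67.5 to 21/67.5). With 31 per arm before loss, the two-sided type I error is about 0.056 to 0.149.

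**5. A real effect, with stoppers not measured.** Assume that 20% of the exercise arm stop and lose all of a 67.5 m benefit. The intention-to-treat effect is 0.8 × 67.5 = 54 m, while continuers alone show 67.5 m; 67.5 / 54 = 1.25. If 10% stop, or if 20% stop and keep half the benefit, the effect is 60.75 m (0.9 × 67.5, or 54 + 0.2 × 33.75), and 67.5 / 60.75 = 1.11. This part does not require stoppers to be less fit.

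**6. Does the imputation repair it?** If discontinuers have no later walk test, every observed exercise-arm outcome comes from a continuer. Imputing from sex, age, group and baseline score gives discontinuers the outcomes of continuers with the same values. Differences already visible in those variables are allowed for; lost benefit and decline after baseline are not.

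**7. The metastasis clause.** The documents give no progression rate. At an assumed 5–15%, 3 to 9 of 62 would be removed (0.05 × 62 = 3.1; 0.15 × 62 = 9.3). If progression is unrelated to arm, loss is equal and the bias is about zero.

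**The case against.** Item 18b does not contain the word only. Its preceding sentence aims at complete follow-up, item 13 plainly requires outcomes from everyone, and the SPIRIT table condenses a fuller protocol. On this view the sentence is loose drafting that sites would not apply literally. Item 10 is an eligibility entry, and no passage says that patients with later metastases leave the analysis set. Some of them may never reach surgery, and so would have no pre-surgery walk test whatever item 10 says.

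Much of this stands. A reader might infer that an intention-to-treat comparison cannot be made at all. The documents do not support that, because item 13 points the other way and item 20c plans a missingness check and conditional imputation. A reader might also infer that the result is biased in favour of exercise. That is not established either: the direction depends on who leaves and from which arm, controls can drop out too, and the plan's 20% drop-out applies to the whole sample. The metastasis clause covers both arms and favours neither by itself.

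What the objection does not remove is the contradiction. Item 13 is the general statement and item 18b the specific one for discontinuers. A site that turns to the specific rule finds only baseline data named.

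**Conclusion.** The point holds as a conflict within the document. Item 18b is at odds with items 13 and 20a. Item 10 is at odds with the main-text criteria and, through its second limb, with intention-to-treat. Followed as written, both permit loss of outcomes after randomisation.

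For item 18b, bias towards exercise is plausible but not certain. For 10–20% exercise-only loss and no true effect, it is about +5 to +21 m if less fit participants leave, zero if loss is unrelated to walking distance, and −5 to −9 m if fitter ones leave. If 20% stop, lose all benefit and go unmeasured, a 54 m effect appears as 67.5 m. The loss fractions, correlations and retained benefit are assumptions; only the SD, the 67.5 m target, the 20% drop-out and the 62 recruited come from the article. For item 10 the harm is that the randomised set is broken, with no direction implied.

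**What to change.** - **Item 18b.** Replace the sentence with: *All scheduled outcome assessments, including the pre-surgery 6MWT, are sought from every randomised participant regardless of adherence or discontinuation, unless consent to follow-up is withdrawn.* This brings it into line with items 13 and 20a.
- **Item 10.** Reconcile it with the Participants section so that the metastasis criterion applies at enrolment only, and keep participants with later metastases in the intention-to-treat set. This concerns eligibility and analysis, not their clinical care.
- **Analysis.** State how participants without a pre-surgery 6MWT, including those who do not reach surgery, are handled.

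The cost is protocol wording plus a few follow-up assessments of discontinuers by the existing assessors; some will decline. The Trial status section reports 29 participants recruited of the 62 planned, so at that point the change could still apply to more than half of the sample.

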**Methods:**

The PERIOP-OG trial is a pragmatic, multi-centre, randomised controlled trial comparing a peri-operative exercise programme with standard care in patients with oesophagogastric cancers treated with NCT and surgery. The intervention group undergo a formal exercise training programme and the usual care group receive standard clinical care (no formal exercise advice). The training programme is initiated at cancer diagnosis, continued during NCT, between NCT and surgery, and resumes after surgery. All participants undergo assessments at baseline, post-NCT, pre-surgery and at 4 and 10 weeks after surgery. The primary endpoint is cardiorespiratory fitness measured by demonstration of a 15% difference in the 6-min walk test assessed at the pre-surgery timepoint. Secondary endpoints include measures of physical health (upper and lower body strength tests), body mass index, frailty, activity behaviour, psychological and health-related quality of life outcomes. Exploratory endpoints include a health economics analysis, assessment of clinical health by post-operative morbidity scores, hospital length of stay, nutritional status, immune and inflammatory markers, and response to NCT. Rates of NCT toxicity, tolerance and compliance will also be assessed.

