### Primary outcome

#### Cardiorespiratory fitness

The primary outcome is measurement of cardiorespiratory fitness using the 6MWT assessed at the pre-surgery timepoint. The 6MWT is performed with participants walking up and down a 20 m course marked by cones for 6 min under instruction to cover as much ground as possible. The number of laps completed is recorded. A standard set of instructions is used as per the European Respiratory Society guidelines. The 6MWT is a validated assessment of cardiorespiratory function in clinical populations [30, 31]. A systematic review in 2016 demonstrated that field tests may be able to predict post-operative outcome; however, further validation work is merited [32].

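### The plan agrees on the pre-surgery visit but contradicts itself on the scale of the primary 6MWT endpoint and on which t-test decides the trial

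*Protocol article*

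**What the plan says.** **Endpoint as a value.** The abstract describes the primary endpoint as "demonstration of a 15% difference in the 6-min walk test assessed at the pre-surgery timepoint". The primary outcome section agrees: "The primary outcome is measurement of cardiorespiratory fitness using the 6MWT assessed at the pre-surgery timepoint".

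**Endpoint as a change.** In Table 2 (SPIRIT), the primary hypothesis in item 7 concerns an "increase in cardiorespiratory fitness assessed using a 6-min walk test between the baseline and the pre-surgery time point". Item 12 reads: "The primary endpoint is cardiorespiratory fitness measured by the 6-min walk test between the baseline assessment and the pre-surgery time point". It then continues: "Secondary endpoints include the measurement of cardiorespiratory fitness".

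**Sample size.** The main text calls the 15% effect a difference. Item 14 calls it a gain in score. Item 14 also supplies the SD of 85 m, attached to the baseline score of 450 m.

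**Analysis.** The main text says: "The primary analysis of the primary outcome will be conducted using t-tests of independent group mean differences in 6MWT". It names no visit. Item 20a says: "The primary analysis of the primary outcome will be conducted as t-tests of independent group mean differences in 6MWT at each time point". Both go on to change-score tests: "Individual change in 6MWT will be calculated from baseline and compared at different time points using t-tests". Item 20a adds chi-squared tests, at several visits, of walking further than the pooled baseline median. Table 1 marks the 6MWT, in its primary endpoint row, at five visits including baseline.

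The article does not state which of these tests decides the trial.

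**The concern.** A single confirmatory claim needs one variable, one visit and one test. Here the visit is clear from the endpoint definitions, but the variable is described in two ways, and the label of primary analysis in item 20a covers a whole set of tests.

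Two things are at stake. First, value and change can give different answers in the same data, because the two estimates differ by the chance imbalance at baseline. If the choice is open when the data are seen, the error rate exceeds 5%. Second, the stated power was computed for one scale and does not transfer automatically to the other. Patients and physiological assessors are unblinded, so a rule fixed in advance matters all the more.

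A baseline t-test, which item 20a's wording includes, tests only chance under randomisation and says nothing about the intervention.

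**Working it through.** **Inputs.** From the sample size section and item 14: baseline 450 m, SD 85 m, effect 15%, p = 0.05, power 80%, 26 participants with full data (read as per group). From Table 1: five 6MWT visits, four of them after baseline. The documents give no between-visit correlation, so it is assumed and varied.

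**1. The plan's own figure.** Effect = 0.15 × 450 = 67.5 m. The standard error of a difference with 26 per group is 85 × √(2/26) = 23.6 m. The exact two-sided 5% t-test needs 25.9, so 26 per group, with power 80.2%. Reading 26 as the total (13 per group) gives 49%, and a one-sided test would need only 20 to 21 per group. The figure therefore belongs to one two-sided test of a score with SD 85 m, 26 per group.

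**2. Power on the change scale.** With equal SDs at both visits and correlation r, SD of change = 85 × √(2(1 − r)). With 67.5 m and 26 per group:

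| r (assumed) | SD of change (m) | Power |
|---|---|---|
| 0.3 | 100.6 | 66% |
| 0.4 | 93.1 | 73% |
| 0.5 | 85.0 | 80% |
| 0.6 | 76.0 | 88% |
| 0.7 | 65.8 | 95% |

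The two scales have the same power only near r = 0.5.

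**3. How far value and change can diverge.** Their estimates differ by the baseline imbalance, whose standard error is also 23.6 m. That is 23.6 / 67.5 = 35% of the target effect.

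**4. Type I error if the choice is open.** Simulation with no effect, 26 per group, five equally correlated normal visits, each test two-sided at 5%, 20,000 trials per correlation:

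| r (assumed) | Pre-surgery value only | Value or change at pre-surgery | Any of four post-baseline score tests |
|---|---|---|---|
| 0.3 | 4.7% | 8.5% | 17.5% |
| 0.5 | 4.8% | 8.9% | 15.3% |
| 0.7 | 4.9% | 9.3% | 12.9% |
| 0.8 | 4.9% | 9.3% | 11.3% |
| 0.9 | 5.0% | 9.7% | 9.6% |

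For reference, four independent tests would give 1 − 0.95⁴ = 18.5%. The second column of error rates needs only the contradiction over scale. The last column needs item 20a's label to be taken as a success rule.

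**The case against.** The strongest reply is that the deciding visit is not in doubt. Every definition of the endpoint names pre-surgery, and so does the primary objective. The Background makes the post-operative programme a secondary aim, so the 4-week and 10-week results serve that aim. The extension to every visit appears only in the SPIRIT table and not in the main-text analysis section. Under randomisation, value and change have the same expected group difference. All of this stands, and it limits the point in four ways.

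- A reader might infer that 5% and 80% do not describe the trial's decision at all. They do describe one reading, the raw pre-surgery score, and the sample size reproduces for it.
- A reader might infer that a trial that misses at pre-surgery may be declared positive on another visit. No passage says so. Item 20a's label leaves it open, while the endpoint definitions and the stated aims point the other way. Counting all eight post-baseline score and change tests would give about 23% to 28%, but no passage makes the change tests success criteria.
- A reader might infer that 80% is wrong for the change score. It is unsupported, not refuted: it is correct near a correlation of 0.5 and too low above that.
- A reader might take item 12's secondary listing of cardiorespiratory fitness as a further contradiction. It plausibly means the 6MWT at the other visits.

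It can also be said that ranking and multiplicity detail belongs in an analysis plan not shown here. That excuses silence. It does not excuse two descriptions of the primary endpoint, or a primary analysis whose wording reaches beyond the primary visit.

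**Conclusion.** The point holds as an internal contradiction about scale and deciding test, with the pre-surgery visit agreed. The stated error rate and power are valid for one test, the raw pre-surgery 6MWT (80.2% with 26 per group).

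If the scale stays open, the type I error at the pre-surgery visit is about 9%, and this figure changes little with the assumed correlation. If item 20a were applied so that any post-baseline score test could count, the error would be about 10% to 17% for assumed correlations of 0.3 to 0.9. Power for a change score cannot be stated from the documents; it is 66% to 95% for assumed correlations of 0.3 to 0.7. These figures rest on normal data, equal SDs of 85 m at each visit, and (for the error rates) one common correlation between visits.

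This concerns the trial's main claim and is wrong as written. It should be settled before any comparison of outcomes.

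**What to change.** State one confirmatory test: the between-group difference in 6MWT at the pre-surgery visit, on the raw score, two-sided at 5%. The raw score is the natural choice because the sample size was computed for it. Then:

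- in item 20a, delete the phrase that extends the primary analysis to every visit, and in the main-text Statistical analysis section name the pre-surgery visit;
- align items 7 and 12, and the effect wording in the sample size section and item 14, with the abstract and the primary outcome section;
- label the post-NCT, 4-week and 10-week comparisons, all change-from-baseline t-tests and item 20a's chi-squared tests as secondary and unable to establish primary success;
- drop the baseline t-test.

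The cost is wording only. The article reports 29 of the planned 62 participants recruited and no interim analysis, so the rule could be fixed before results are compared. The downside is that a significant result at another visit or on another scale can no longer be presented as the primary result. Keeping all four post-baseline score tests as alternatives would cost more: Bonferroni at 0.05 / 4 = 0.0125 needs about 37 completers per group, and 26 per group would give 61% power for any single test.
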